### Concealment mechanism {16b}

After confirming that the participants are qualified, the envelopes are opened sequentially, and the participants are assigned to their respective groups. Those responsible for generating the random assignments will not be participating in the trial.

### Implementation {16c}

The statistician independent of the trial will generate the allocation sequence, physicians will enroll participants, and the nurse will assign participants to interventions.

## Assignment of interventions: blinding

### Who will be blinded {17a}

This is a single-blind randomized controlled trial in which the researchers responsible for patient assessment and data collection will be unaware of the intervention allocations.

### Procedure for unblinding if needed {17b}

This study will not involve unblinding procedures.

## Data collection and management

### Plans for assessment and collection of outcomes {18a}

An outcomes assessor will measure the results before and after the intervention, followed by a 12-week follow-up. The study intervention will be conducted at AMDI, USM, and patients will be registered at the exercise clinic at AMDI, USM.

### Plans to promote participant retention and complete follow-up {18b}

Provide participants with a comprehensive overview of the study timeline and emphasize the importance of their continued participation. Moreover, regular reminders will be sent to participants via email, text messages, and phone calls to facilitate timely scheduling and encourage their attendance at upcoming follow-up assessments.

### Data management {19}

All data forms and original laboratory records collected during the study will be stored in lockable filing cabinets within the office in AMDI. Additionally, digital data will be stored on the researcher’s official work desktop computer, accessible only through a password-protected login. All data will be maintained for 7 years.

### Confidentiality {27}

All study data will be securely stored in password-protected electronic databases, accessible only to authorized personnel involved in the research. Personal identifiers will be replaced with unique study identification codes to anonymize participant information. Physical documents containing participant data will be stored in locked cabinets in a restricted-access area.

### Plans for collection, laboratory evaluation, and storage of biological specimens for genetic or molecular analysis in this trial/future use {33}

The excess/leftover blood specimens will be stored for 2 years and discarded after this period. The blood specimen will not be used for other research during the storage period.

## Statistical methods

### Statistical methods for primary and secondary outcomes {20a}

All data will be analyzed using SPSS version 29. One-way ANOVA will be used to evaluate whether there were significant differences in age, gender, and symptom severity of gout between the intervention and control groups. Two-way repeated measures ANOVA will be used to analyze differences in outcomes before and after treatment. The significance level will be set at *p* < 0.05. If some patients are unable to complete the experiment due to uncontrollable factors or if they violate the inclusion criteria during the study, these patients will be excluded from the analysis.

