##### Intervention group (exergames + ice therapy)

Participants in the intervention group will be asked to receive an exergames intervention for 40 min a day, 3 to 5 days a week, at least 120 min per week, for 4 weeks. The target HRmax should be between 64 and 76% for moderate exercise intensity. Exergames intervention will be facilitated by cardio-respiratory exercise games (Ring Fit Adventure, Mario Tennis Aces, Sports Party, Fit’s Island Cycling, and Aerobic Step) from Nintendo. Participants must wear a heart rate monitor during exercise to achieve the target heart rate. In addition to applying heart rate as an objective indicator of exercise intensity, the Borg Rating of Perceived Exertion (RPE) will be applied to measure the individual’s perception of exercise intensity. Participants will be asked to achieve moderate-intensity exercise on a Borg scale of 10 to 13.

Moreover, the patients will also be treated with ice therapy, utilizing circular localized massage with ice bags made of polyethene plastic on key muscles of the upper and lower extremities that are prone to muscle damage and lactic acid accumulation during exercise as well as on critical joints prone to gout attacks. The duration of ice therapy will be 15 to 20 min after exergames intervention.

To rule out the influence of dietary choices, the researchers will ask all participants to maintain a low-purine diet and abstain from alcohol during the exercise intervention. Moreover, participants will be asked to record their daily intake in diaries. The researcher will regularly monitor and check the diaries to ensure adherence to dietary guidelines.

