### Outcomes {12}

The primary and secondary outcomes of the study will be measured at three time points: baseline (0 weeks), post-intervention (4 weeks), and follow-up (12 weeks). All measurements will be taken at the same location and performed by the same therapist. All data will be collected by a designated investigator and recorded in Microsoft Excel.

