#### Secondary outcomes

Anthropometric parameters: waist circumference (WC), hip circumference (HC), waist-to-hip ratio, range of movement in target joinBiochemical indicators: fast blood glucose, total cholesterol (TC), triglyceride, high-density lipoprotein (HDL) cholesterol, low-density lipoprotein (LDL) cholesterol, uric acid (UA), and creatininePhysiological indicators: systolic blood pressure (SBP), diastolic blood pressure (DBP)Subjective indicators: pain intensity (24 h after exercise, measurement tool: visual analogue scale (VAS)), gout-specific quality of life (measurement tool: The Gout Impact Scale (GIS)), kinesiophobia (measurement tool: The Tampa Scale of Kinesiophobia (TSK)), positive and negative affect of exercise (measurement tool: Positive and Negative Affect Schedule (PANAS))Adverse effect: rate of gout flare

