### Methods in analysis to handle protocol non-adherence and any statistical methods to handle missing data {20c}

In this study, intention-to-treat (ITT) analysis will be employed to assess the trial policy regarding the treatment received by allocated participants, while per-protocol (PP) analysis will be utilized to exclude or scrutinize participants deviating from the treatment protocol. This study anticipates minimal or no occurrence of missing outcome data, as the trial will not be terminated before all data is collected.

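### The planned repeated-measures ANOVA is not tied to a named between-arm contrast, does not use baseline as a covariate, and excludes non-completers despite an ITT promise

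*Protocol article*

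**What the plan says.** All points are from the protocol article.

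- **Outcome analysis**, Statistical methods {20a}: "Two-way repeated measures ANOVA will be used to analyze differences in outcomes before and after treatment". No group-by-time term, arm difference, deciding visit or baseline covariate is named.
- **Baseline comparison**, same section: "One-way ANOVA will be used to evaluate whether there were significant differences in age, gender, and symptom severity of gout" between the arms.
- **Analysis set**, same section: for patients who cannot complete, or who are found to breach the inclusion criteria during the study, "these patients will be excluded from the analysis". Section {20c} says that "intention-to-treat (ITT) analysis will be employed", with a per-protocol analysis beside it. It adds: "This study anticipates minimal or no occurrence of missing outcome data".
- **Visits**, Outcomes {12}: primary and secondary outcomes are measured at weeks 0, 4 and 12.
- **Comparison**, sections {6b} and {11a}: exergames plus ice against exergames alone, with the same exergames programme in both arms. In addition, "the researchers will ask all participants to maintain a low-purine diet and abstain from alcohol during the exercise intervention".
- **Flares**, Secondary outcomes: "rate of gout flare" is listed as an adverse effect. {20a} covers primary and secondary outcomes and gives no other method for it.

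**The concern.** Only the contrast between arms is randomised. Exercise, diet and abstinence from alcohol act in both arms. Patients with no or mild pain are excluded, so pain scores are also likely to fall through regression to the mean. A before-after difference therefore says little about ice. A two-way repeated-measures ANOVA yields three tests (group, time, group by time), and the plan does not say which one carries the conclusion.

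Three further weaknesses follow from the method:

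- Baseline enters as one of the repeated responses, which usually costs precision compared with using it as a covariate.
- With three visits the interaction has 2 degrees of freedom. It can show that the arms' profiles differ, but not by how much or at which visit.
- The classical form uses only participants with every visit. The exclusion sentence in {20a} says much the same in words, and {20c} promises the opposite.

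At stake are the clarity of the main conclusion, some precision in a trial with about 14 evaluable patients per arm, and the protection that analysing participants as randomised gives.

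**Working it through.** **Inputs.** From Sample size {14}: effect size 0.25 (type not stated), two-sided alpha 0.05, power 80%, serum uric acid SD 100 µmol/L, 14 per arm (N = 28), 10% dropout, 30 recruited. From {12}: m = 3 visits. The correlation ρ between visits is not in the document, so it is an assumption shown over 0.3 to 0.8. Equal variances and equal correlations between visits are also assumed.

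**Step 1: the plan's own figure.** Read 0.25 as Cohen's f for the group-by-time interaction, with k = 2 arms and ρ = 0.5:

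- λ = f² × N × m / (1 − ρ) = 0.0625 × 28 × 3 / 0.5 = 10.5
- df1 = (k − 1)(m − 1) = 2; df2 = (N − k)(m − 1) = 52
- Power = 0.812 at N = 28 and 0.778 at N = 26

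So N = 28 is reproduced. Other readings do not give it: the between-group main effect needs 86 in total, a two-visit interaction needs 34, and a two-sample comparison at d = 0.25 needs 252 per arm.

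**Step 2: effect of excluding non-completers.** 30 × 0.9 = 27, below 28, and interaction power falls to 0.795. Keeping 28 complete would need 28 / 0.9 = 31.1, so 32 with equal arms.

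**Step 3: detectable difference, like for like.** Take 14 per arm and an arm difference of d SDs, equal at weeks 4 and 12 and zero at baseline.

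- *Planned interaction:* for the pattern (0, d, d), f² = d²/18, so λ = (d²/18) × 28 × 3 / (1 − ρ). Solve for 80% power with 2 and 52 df.
- *Baseline adjustment at one visit:* the residual variance is (1 − ρ²), so d = 1.102 × √(1 − ρ²). Here 1.102 is the standardised difference detectable with 80% power at 14 per arm and 25 df.

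| Assumed ρ | Planned interaction, µmol/L | Baseline-adjusted, µmol/L | Reduction |
|---|---|---|---|
| 0.3 | 124 | 105 | 15% |
| 0.5 | 105 | 95 | 9% |
| 0.7 | 81 | 79 | 3% |
| 0.8 | 66 | 66 | none |

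**Step 4: a growing effect.** Suppose the difference at week 4 is half that at week 12. At ρ = 0.5 the planned interaction has 80% power for a week-12 difference of 1.21 SD. A week-4 adjusted contrast would then have 43% power (48% at ρ = 0.3 and 38% at ρ = 0.7). The choice of visit therefore matters.

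**Step 5: the analysis-set passages side by side.** {20a} removes non-completers and eligibility violators from the analysis without limiting this to one population. {20c} promises ITT and keeps removal of deviators for the per-protocol analysis. As an ITT rule the {20a} sentence cannot stand.

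**The case against.** The strongest reply is that a two-way repeated-measures ANOVA is a legitimate analysis of a parallel-group trial. Its second factor is arm, and its interaction asks whether change differs between arms, which is the randomised question. The stated N = 28 comes out exactly under that test, so the authors probably had it in mind. The trial calls itself exploratory, and a condensed article may leave the tested term to a fuller document. Baseline adjustment is then an improvement, not the correction of an error, and its gain shrinks to nothing at high correlation.

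Most of this stands. A reader might infer that the plan uses an invalid test, or one aimed only at change over time. The documents do not support that, and nothing in them says that a time effect will be reported as efficacy. A reader might also quote a larger precision loss by assuming that the effect grows to week 12. Those would be week-12 differences, and they cannot be set against a week-4 contrast, which does worse than the plan in that scenario.

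What the reply does not remove is the wording of {20a}, which points to before-after differences and fixes no between-arm estimate, and the conflict between its exclusion sentence and {20c}. That conflict is in the text and does not depend on how any software handles missing visits.

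**Conclusion.** The planned analysis is valid but inefficient, and its conclusion is not tied to a between-arm estimate. The like-for-like precision loss for serum uric acid runs from 15% at ρ = 0.3 to none at ρ = 0.8. It rests on SD 100, 14 per arm, an equal effect at both post-baseline visits and an assumed ρ. The shortfall from excluding non-completers is small in power terms (27 against 28; 0.795 against 0.812, at ρ = 0.5). The contradiction with ITT is the weightier part of that point.

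Two minor points sit beside this. A flare rate is an event outcome that repeated-measures ANOVA suits poorly. One-way ANOVA does not suit gender, and significance tests of baseline balance are uninformative after randomisation. A reader might take these as faults of the primary analysis. They are not: flares are secondary, and gender belongs to the separate baseline sentence.

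This should be changed before outcomes are analysed by arm.

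**What to change.** 1. Analyse each continuous outcome with a linear mixed model on weeks 4 and 12, with arm, visit, arm by visit and the baseline value as covariate. Include all randomised participants with any post-baseline value.
2. Base the conclusion on the adjusted arm difference with 95% CI at one visit named in advance. Week 4, the end of the intervention, is a natural choice; its cost is lower power if the effect grows to week 12. Report within-arm changes descriptively.
3. Remove the exclusion sentence in {20a} from the ITT analysis and keep it for the per-protocol analysis only.
4. Compare flare rates between arms with an exact or Poisson method.
5. Replace the one-way ANOVA baseline tests, including the one on gender, with a descriptive table.

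The cost is wording only. The baseline values are already collected, and the SPSS version named in the plan has a mixed-model procedure. No extra patients, visits or measurements are needed.

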Exergames technology has been widely recognized in rehabilitation and has achieved positive results [34]. Fitness games used for therapeutic purposes, also known as serious games, can provide patients with an immersive experience that allows them to focus on training and achieve more optimal results in challenging and competitive programs [35]. Exergames typically provide light to moderate exercise training to help users burn calories. Studies have demonstrated the beneficial effects of exergames as an aid in weight loss [36]. Moreover, few studies report adverse events in exergames, and the safety of exergames is widely recognized [37]. However, the long-term effects of exergames need to be supplemented and verified by future research [36].

To our knowledge, no study has investigated the effect of exergames and ice therapy among gout patients. However, research evidence supports that exergames can improve persistence and significantly reduce BMI. Ice therapy can increase the patient’s adherence to exercise by reducing symptoms and joint responses after exercise, thereby assisting in better reducing BMI. Therefore, this study aims to examine the combined effect of exergames and ice therapy in patients with gout in Pulau Pinang. This study is expected to demonstrate that exergames combined with ice therapy are more effective in gout management compared to exergames alone. The outcome of this study could be used as guidelines for choosing the right exercise program to improve the health status of the gout population. This study would also benefit patients with gout by highlighting any gaps between their awareness and the correct concepts of gout management, encouraging them to prioritize exercise. The findings of this study may help healthcare practitioners re-evaluate gout treatments to identify and address deficiencies in current approaches to gout management, and establish a new program and perspective for gout management.

However, this study has some major scopes. Since no studies have reported the optimal exercise intensity and frequency for patients with gout, this study does not account for the potential effects of different intensities and frequencies of exercise. Moreover, as this study only included patients from Pulau Pinang, the findings may lack universality.

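### The outcome analysis excludes some randomised patients although the plan states ITT, and read literally the exclusion can depend on BMI, a primary outcome

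*Protocol article*

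**What the plan says.** All references are to the protocol article.

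- Statistical methods for primary and secondary outcomes {20a} names a two-way repeated measures ANOVA and ends with an exclusion rule. The rule first names patients whom uncontrollable causes keep from completing, and then continues: "if they violate the inclusion criteria during the study, these patients will be excluded from the analysis". No analysis set is named, so the rule attaches to the main analysis of all outcomes.
- Section {20c}, on non-adherence and missing data, says "In this study, intention-to-treat (ITT) analysis will be employed" and, separately, "per-protocol (PP) analysis will be utilized to exclude or scrutinize participants deviating from the treatment protocol". It adds: "This study anticipates minimal or no occurrence of missing outcome data". The reason given is that the trial will not be terminated before the data are collected.
- Inclusion criteria: BMI of at least 25. Primary outcomes: BMI and serum uric acid (SUA).
- Sample size {14}: 28 patients raised to 30 for 10% dropout.
- Adverse event reporting and harms {22}: a patient with any intervention-related adverse event is withdrawn from the trial.

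**The concern.** Two different analysis populations are prescribed for the same outcomes. A randomised patient who has to stop for an outside reason is dropped under {20a} and kept under {20c}. With nothing to say which governs, the choice could be made after the data are seen. With 15 patients per arm, a few patients in or out can matter.

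The second limb of the {20a} rule raises a further problem. One inclusion criterion is a threshold on a variable that the intervention is meant to lower. If a later BMI below 25 counts as violating that criterion, being analysed depends on the primary outcome, and the arm with more weight loss loses more of its responders. The randomised comparison is then no longer between the groups as allocated.

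**Working it through.** **1. The two sections side by side (no arithmetic).**

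| Randomised patient | {20a} | {20c}, ITT | {20c}, per-protocol |
|---|---|---|---|
| Cannot complete, outside cause | excluded | included | depends on deviation |
| Ceases to meet an inclusion criterion | excluded | included | depends on deviation |
| Deviates from treatment only | not addressed | included | excluded or scrutinised |

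The first two rows conflict. The per-protocol analysis does not resolve them, because {20a} states its rule for the outcome analysis as a whole.

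**2. The plan's own numbers.** N = 28 reproduces as the group-by-time test of a repeated measures ANOVA. The plan gives effect size 0.25, alpha 0.05, two groups and three visits. I assume that 0.25 is Cohen's f, that the correlation between visits is 0.5, and that sphericity holds.

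- Noncentrality = f² × N × m / (1 - rho) = 0.0625 × 28 × 3 / 0.5 = 10.5, on 2 and 52 degrees of freedom; power 81.2%.
- All 30 analysed: noncentrality 11.25; power 84.1%.
- The planned 10% lost: 30 × 0.9 = 27; power 79.5%.

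So the sample size section does allow for loss, while {20c} expects almost none.

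**3. What the BMI reading would do.** The document gives no BMI distribution, so these inputs are assumptions: baseline BMI normal with SD 3 and centre 27, 28 or 30, truncated at 25; mean change -0.5 in one arm and -1.0 in the other; SD of change 0.7; one post-treatment visit; anyone below 25 at that visit removed.

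For mean change d, the share removed is the average, over baseline values b in the truncated distribution, of Φ((25 - b - d) / 0.7). The between-arm differences were obtained by simulation before and after removal.

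| Centre | Removed, change -0.5 | Removed, change -1.0 | Post-treatment difference (true -0.50) | Difference in change (true -0.50) |
|---|---|---|---|---|
| 27 | 9.4% | 16.4% | -0.26 | -0.48 |
| 28 | 6.8% | 12.0% | -0.30 | -0.48 |
| 30 | 2.8% | 5.3% | -0.38 | -0.49 |

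In an arm of 15, this is 0.4 to 1.4 patients (2.8% to 9.4% of 15) against 0.8 to 2.5 (5.3% to 16.4% of 15).

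The post-treatment difference loses 24% to 48% of its size (0.12/0.50 to 0.24/0.50). The difference in change, which the group-by-time term tests, loses about 2% to 5%. If both arms change equally, the same share is removed from each and neither comparison is biased.

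**The case against.** The strongest reply is that the BMI consequence is only one reading. Violating inclusion criteria during the study could mean ineligibility discovered late, or breach of a criterion such as staying in the local area. That is plausible and may be what the sponsor meant, but the text does not say so and the literal wording covers BMI. It is fair to add that the distortion of BMI change is small, that SUA (the outcome used for sample size) is not an eligibility criterion, and that the trial calls itself exploratory. These points limit the size of the BMI problem. They do not remove the conflict between {20a} and {20c}.

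A reader might infer more than the document supports:

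- *That non-adherent patients are deleted, and with them the effect under study.* The Discussion does expect ice to raise "adherence to exercise by reducing symptoms and joint responses after exercise, thereby assisting in better reducing BMI". But {20a} covers only non-completion from uncontrollable causes. The criteria for discontinuing or modifying interventions {11b} concern the allocated intervention, not the end of outcome measurement.
- *That {20c} justifies the exclusion by expecting little missing data.* It does not link the two. Planning for 10% dropout while expecting little missing data is a tension, not a strict contradiction.
- *That intolerant patients would be lost mainly from one arm.* Nothing in the document supports a direction.
- *That a particular shift in mean SUA can be attached to the rule.* That would need an arbitrary number of dropouts and an arbitrary difference between them and the rest.

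**Conclusion.** The contradiction is established from the text alone: {20a} prescribes an analysis that is not ITT, and {20c} prescribes one that is. The possible dependence on BMI follows from the literal wording and is avoidable. Its size rests entirely on the assumed BMI distributions and changes: removal of about 3-9% against 5-16%, marked attenuation of the post-treatment BMI difference, slight attenuation of the difference in change, and no bias without a true effect. The rule should therefore not be described as able to create a BMI effect through bias. The primary analysis population needs to be settled before the data are analysed.

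**What to change.** 1. Delete the last sentence of {20a}, or confine it explicitly to the per-protocol set.
2. State that the primary analysis includes every randomised participant in the allocated arm, whatever their completion, adherence or later BMI, and uses all observed visits. A mixed model is one way to do this; repeated measures ANOVA drops any case with a missing visit and would bring the exclusion back.
3. Define the per-protocol set by delivery of the intervention, never by later BMI.
4. Align the missing-data expectation in {20c} with the 10% dropout in {14}. That the trial will not stop early does not address dropout by individual patients.
5. Reconcile the withdrawal from the trial described in {22} with the collection of outcomes that an ITT analysis needs.

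Cost: wording changes and slightly more analysis work, with no additional patients. Patients withdrawn early contribute only the visits observed, unless their follow-up continues.
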